#### Out-hospital follow-up

This phase starts if the patient is discharged from the hospital or 30-days have passed since inclusion to the study (whenever earlier; T_2_, maximum 90 days after T_0_) (Table 5). We will determine their status via telephone contact. We will also evaluate hospitalized patients’ situations by consulting their MRN in the recruiting center. We will consider a patient lost to follow-up if we cannot reach them via telephone contact by the end of this phase.

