## Methods and analysis

### Study design and setting

This protocol describes a multicenter, prospective observational cohort study evaluating the prognostic accuracy of qSOFA score, SIRS criteria, and EWSs (NEWS/NEWS2/MEWS) for in-hospital mortality among adult patients presenting to the ED with suspected infection (NCT05172479). The study’s outlines are shown in Fig 1. The study duration is 12 months per center (9 months for recruitment and 3 months for follow-up). Recruiting centers and recruitment status are shown in Table 3 (July 2023).

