#### In-hospital follow-up

Once enrolment is completed, the in-hospital follow-up phase will start (T_1_, maximum 30 days after T_0_) (Table 5). Study team will monitor hospitalized patients’ status (i.e., death, alive and either discharged, transferred to another hospital, or still hospitalized) by consulting their specific medical registration number (MRN) in the recruiting center.

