### Study outcome

The primary outcome of this study is 30-days in-hospital mortality. Secondary outcomes include ICU admission (within 30-days), ICU length of stay, and all-cause mortality within 30 and 90 days.

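### For discharged patients the telephone is the only stated route to vital status, and no contact by day 90 counts as loss, so 30- and 90-day all-cause mortality are open to loss that depends on the outcome

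*Protocol article*

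**What the plan says.** The out-hospital phase begins at discharge or at day 30, whichever comes first, and lasts at most 90 days from enrolment. For this phase the Protocol article (Out-hospital follow-up) says: "We will determine their status via telephone contact". It adds a record check for one group: "We will also evaluate hospitalized patients’ situations by consulting their MRN in the recruiting center". It then defines loss: "We will consider a patient lost to follow-up if we cannot reach them via telephone contact by the end of this phase".

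The outcomes that depend on this phase are secondary: "all-cause mortality within 30 and 90 days" (Study outcome). Table 5 assigns both to the out-hospital phase. The primary outcome does not depend on it: "The primary outcome of this study is 30-days in-hospital mortality" (Study outcome), with status during the stay found "by consulting their specific medical registration number (MRN) in the recruiting center" (In-hospital follow-up).

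On timing, Study design and setting says: "The study duration is 12 months per center (9 months for recruitment and 3 months for follow-up".

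On analysis, Sample size allows 20% for loss and missing data together. Statistical analysis names Kaplan-Meier for 90-day mortality, complete cases if less than 5% is missing, and multiple imputation otherwise.

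**The concern.** The event being counted is death, and the rule for loss is failure to make contact by telephone. A household where the patient has died is plausibly harder to reach than one where the patient is alive. If so, being lost carries information about the outcome.

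None of the planned analyses handles this. Complete-case analysis and standard imputation assume that, given the observed data, missingness is unrelated to vital status. Kaplan-Meier assumes that censored patients have the same later risk as those still followed. With outcome-dependent loss these assumptions fail, and the data collected cannot show by how much.

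At stake are the two all-cause mortality outcomes and the 90-day Kaplan-Meier curve. The rule also makes little use of a source the centres already hold. Under Patient confidentiality, each lead investigator keeps a list linking patients to their record numbers, yet the text does not say that the record is consulted before a discharged patient is called lost.

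**Working it through.** **The plan's own figure.** Sample size cites 74 events in 879 patients, a rate of 74/879 = 8.42%. Then 200/0.0842 = 2375.7, and 2375.7 × 1.20 = 2850.8, which rounds up to the stated 2851. The figure reproduces. It fixes the scale of the calculation but neither supports nor refutes the point.

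**Inputs from the document.** N = 2851. In-hospital deaths at the planning rate: 2851 × 0.0842 = 240, or 8.42% of N, taken as fully known from the record. The other 2851 − 240 = 2611 patients, 91.58% of N, are treated as followed by telephone. Any still hospitalized after day 30 are checked by record, so this slightly overstates exposure.

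**Assumed inputs.** The document gives none of these:
- d, mortality by day 90 among the 2611: 4% or 8%
- k, how many times as likely loss is in those who die as in survivors: 2 or 3
- L, overall loss among the 2611: 20%. This borrows the plan's allowance, which covers loss and missing data together, so it is an upper case.

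**Formulas.**
- Loss in survivors: ls = L / (1 − d + k·d). Loss in deaths: ld = k·ls.
- Observed mortality after discharge: q = d(1 − ld) / (1 − L).
- True 90-day mortality: 8.42% + 0.9158·d.
- Kaplan-Meier, lost patients censored at discharge: 8.42% + 0.9158·q.
- Lost patients dropped: (240 + 2611·d·(1 − ld)) / (240 + 2611·(1 − L)).

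For d = 4%, k = 2: ls = 0.20/1.04 = 19.2% and ld = 38.5%. Deaths after discharge are 2611 × 0.04 = 104, of which 40 go unrecorded. q = 0.04 × 0.615/0.80 = 3.1%. Kaplan-Meier gives 8.42 + 0.9158 × 3.08 = 11.2% against a true 8.42 + 3.66 = 12.1%. Dropping lost patients gives (240 + 64)/(240 + 2089) = 13.1%.

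| d | k | ls / ld | deaths unrecorded | q | true 90-day | Kaplan-Meier | lost dropped |
|---|---|---|---|---|---|---|---|
| 4% | 2 | 19.2 / 38.5% | 40 of 104 | 3.1% | 12.1% | 11.2% | 13.1% |
| 4% | 3 | 18.5 / 55.6% | 58 of 104 | 2.2% | 12.1% | 10.5% | 12.3% |
| 8% | 2 | 18.5 / 37.0% | 77 of 209 | 6.3% | 15.7% | 14.2% | 16.0% |
| 8% | 3 | 17.2 / 51.7% | 108 of 209 | 4.8% | 15.7% | 12.8% | 14.6% |

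The Kaplan-Meier shortfall is 0.8, 1.6, 1.6 and 2.9 points. Dropping lost patients gives too high a proportion in three of the four rows, because the 240 recorded deaths stay in while about 522 patients leave the denominator, most of them survivors.

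**Smaller loss.** The shortfall is 0.9158 × (d − q). Over the same d and k it runs from 0.4 to 1.3 points at L = 10%, and from 0.2 to 0.6 points at L = 5%. With equal loss (k = 1), q = d and Kaplan-Meier has no bias.

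**The case against.** The strongest objection is that higher loss in deaths is an inference. The document gives no loss rate by vital status, and determining status by telephone for a death outcome makes most sense if a relative may answer. Contact information is collected at enrolment, and call attempts, proxy numbers and contact windows may stand in the full protocol that the article condenses. This stands as a limit on size and certainty. It does not remove the point, because the article states a rule for loss that rests on the telephone alone.

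Several stronger readings are tempting, and the documents do not support them:
- *All-cause mortality will be understated.* The direction depends on the estimator. Kaplan-Meier falls if deaths are lost more often, but dropping lost patients can raise the overall proportion.
- *About 40–55% of the deaths go missing.* The working's 37–56% applies to deaths after discharge, at 20% loss. The listed outcomes also include the roughly 240 recorded deaths.
- *A patient readmitted to the same centre who dies there must be classed as lost.* The record check for hospitalized patients sits within this phase, and nothing excludes readmissions. The loss rule simply does not settle the case.
- *No call can establish status at day 90.* No call date is given, and a call on day 90 fits the text. It is fair to say that the stated follow-up leaves little or no margin after day 90 for the last recruits.
- *The accuracy of the scores is distorted.* If loss depended on vital status alone, sensitivity, specificity and AUC among discharged patients would be unchanged, while predictive values and calibration would move. Whole-cohort figures could shift because in-hospital deaths are never lost, or if loss also depends on score. The documents give nothing from which to size either.

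**Conclusion.** The point holds as a risk built into a stated rule and is confined to two secondary outcomes. As written, a discharged patient's vital status rests on telephone contact by day 90, and loss may therefore depend on death in a way the planned analyses do not correct.

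The likely effect is under-counting of deaths after discharge and a 90-day Kaplan-Meier estimate about 1 to 3 percentage points too low. That rests on three assumptions: 20% loss, 4–8% later mortality, and loss two to three times as likely in deaths. It shrinks roughly in proportion to the loss and vanishes if loss is equal. No separate figure can be given for 30-day mortality, since the document says nothing about when deaths after discharge occur. The primary outcome and the sample size built on it are not affected.

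**What to change.** Amend Out-hospital follow-up as follows:
1. Hold a final status check on or shortly after day 90, and consult the recruiting centre's record for every patient at that check, not only those in hospital.
2. Accept a relative's report of death by telephone.
3. Record the date of death or the date last known alive, and censor at the latter.
4. Call a patient lost only when both the record and the telephone fail.
5. Add a sensitivity analysis that bounds the result by counting lost patients as all alive and then as all dead.

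The bounds do not replace the record check. Their width is the number lost divided by 2851: 522/2851 = 18.3 points at 20% loss, against 131/2851 = 4.6 points at 5%. They are informative only once loss has been brought down.

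The cost is one record look-up per discharged patient, by staff who already hold the list of record numbers, and a short window after day 90 at each centre. No extra patients or procedures are needed.

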### Study outcome

The primary outcome of this study is 30-days in-hospital mortality. Secondary outcomes include ICU admission (within 30-days), ICU length of stay, and all-cause mortality within 30 and 90 days.

### Predictors

Lead investigator in each center will extract the demographics, components of CCI, vital signs, and blood investigations from the medical record of each potentially eligible patient. Study team will use the patient’s initial vital signs, level of consciousness (i.e., first measurement in triage), WBC count, and partial pressure of carbon dioxide (pCO_2_) to calculate qSOFA, SIRS, and EWSs. Blood pressure will be measured by using an electronic sphygmomanometer and results will be recorded in millimeters of mercury (mmHg). MAP will be calculated from SBP and diastolic blood pressure (DBP) using the following equation:

$$MAP=\frac{SBP+2(DBP)}{3}$$

Pulse rate (recorded as beats/min) and oxygen saturation (recorded as a percentage) will be measured using an electronic pulse oximetry device. We will report whether the oxygen saturation reading was in room air or while a patient is on oxygen therapy. Body temperature will be measured orally or (axillary if necessary) by electronic thermometer and recorded as degree Celsius. A new-onset Glasgow Coma Scale (GCS) score of <15 will be considered significant for qSOFA calculation. If it is unclear whether a patient’s confusion is ‘new’ or their usual state, we will assume the altered mental state/confusion is new until confirmed otherwise for all scores calculation.

Initial WBCs count (recorded in x10^9^/μL) and pCO_2_ (recorded in mmHg; if available) will be obtained from the patient’s medical record and entered into the eCRF.

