Altered mental status (GCS <15)	Yes	1	—	—
Heart rate (beats/min)	—	—	>90	1
Respiratory rate (breaths/min)	≥22	1	>20	1
Systolic blood pressure (mm Hg)	≤100	1	—	—
Temperature (°C)	—	—	<36 or >38	1
White blood cells count (x10^9^/μL)	—	—	<4 or >12 or >10% bands	1
	**Maximum score**	**3**	**Maximum score**	**4**
	**Positive cut-off value**	**≥2**	**Positive cut-off value**	**≥2**

***GCS*:** Glasgow Coma Scale; ***qSOFA*:** quick Sequential Organ Failure Assessment; ***SIRS*:** Systemic inflammatory response syndrome.

**Table 2 pone.0281208.t002:** Components of NEWS, NEWS2, and MEWS.

Variable	NEWS		NEWS2		MEWS	
	*Cut-off*	*Points*	*Cut-off*	*Points*	*Cut-off*	*Points*
AVPU	Alert	0	Alert	0	Alert	0
	VPU	3	CVPU*	3	React to voice (V)	1
	—	—	—	—	React to pain (P)	2
	—	—	—	—	Unresponsive (U)	3
HR (beats/min)	51–90	0	51–90	0	51–100	0
	91–110; or 41–50	1	91–110; or 41–50	1	41–50 or 101–110	1
	111–130	2	111–130	2	<40 or 111–129	2
	≤40 or ≥131	3	≤40 or ≥131	3	≥130	3
O_2_Sat (%)	≥96	0	≥96^†^	0	—	—
	94–95	1	94–95	1	—	—
	92–93	2	92–93	2	—	—
	≤91	3	≤91	3	—	—
Oxygen supp.	No	0	No	0	—	—
	Yes	2	Yes	2	—	—
RR (breaths/min)	12–20	0	12–20	0	9–14	0
	9–11	1	9–11	1	15–20	1
	21–24	2	21–24	2	<9 or 21–29	2
	≤8 or ≥25	3	≤8 or ≥25	3	≥30	3
SBP (mm Hg)	111–219	0	111–219	0	101–199	0
	101–110	1	101–110	1	81–100	1
	91–100	2	91–100	2	71–80 or ≥200	2
	≤90 or ≥220	3	≤90 or ≥220	3	≤70	3
Temperature (°C)	36.1–38	0	36.1–38	0	35–38.4	0
	35.1–36 or 38.1–39	1	35.1–36 or 38.1–39	1	<35 or ≥38.5	2
	≥39.1	2	≥39.1	2	—	—
	≤35	3	≤35	3	—	—
	**Maximum score**	20	**Maximum score**	20	**Maximum score**	14
	**Positive cut-off value**	≥5	**Positive cut-off value**	≥5	**Positive cut-off value**	≥5

***AVPU*:** Alert, verbal, pain, or unresponsive; ***HR*:** Heart rate; ***NEWS*:** National early warning score; ***NEWS2*:** National early warning score 2; ***MEWS*:** Modified early warning score; ***O***_***2***_***Sat*:** Oxygen saturation; ***RR*:** Respiratory rate; ***SBP*:** Systolic blood pressure.

*—Level of consciousness and new confusion (‘C’), thus AVPU becomes ACVPU, where C represents new confusion.

†—NEWS2 has a dedicated section (SpO_2_ Scale 2) for use in patients with hypercapnic respiratory failure who have clinically recommended oxygen saturation of 88–92%.

The 2016 SCCM/ESICM task force recommended using qSOFA [11], while the 2021 Surviving Sepsis Campaign strongly recommended against its use compared with SIRS, NEWS, or MEWS as a single screening tool for sepsis or septic shock [14].

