### PASSEM study versus original derivation cohorts

The key characteristics of PASSEM Study and the original derivation cohorts of qSOFA, SIRS, and EWSs that will be assessed are shown in Table 4.

**Table 4 pone.0281208.t004:** Characteristics of PASSEM study and the original development cohorts of qSOFA score, SIRS criteria, NEWS/NEWS2, and MEWS.

Characteristic	PASSEM (n = 2,851)	qSOFA (n = 1,309,025)	SIRS (n = 519)	NEWS/NEWS2 (n = 35,585)	MEWS (n = 709)
**Data collection period**	2021–2022	2010–2012	1992	2006–2008	2000
**Study design**	Prospective cohort	Retrospective cohort	Prospective cohort	Retrospective cohort	Prospective cohort
**Setting**	30 EDs across 7 countries	12 community and academic hospitals in southwestern Pennsylvania (ED, hospital ward, and ICU)	42 ICUs in 40 US hospitals	MAU at Portsmouth hospitals NHS Trust, UK	MAU at District General Hospital (DGH), UK
**Definition of infection**	Based on opinion of attending ED physician	Combination of body fluid culture and nonprophylactic antibiotic administration in the EHR	NA	NA	NA
**Inclusion criteria**	Adult patients (age ≥18 yrs.) with suspected infection who presented to the ED and planned for hospitalization	Adult patients (age ≥18 yrs.) with suspected infection	Patients with sepsis who lack a clear source of infection	All general medical emergency patients aged ≥16 yrs., except for those transferred directly to critical care areas of the hospital	All medical emergency admissions admitted to the MAU
**Primary outcome**	30-days in-hospital mortality	In-hospital mortality	24-hours in-hospital mortality	24-hours in-hospital mortality	HDU or ICU admission, attendance of the cardiac arrest team at a cardiorespiratory emergency and death at 60 days
**Time window for measuring variables**	Initial presentation (at triage)	From 48 hrs. before to 24 hrs. after the onset of infection	Upon admission to ICU	NA	Twice daily for up to 5 days

***ED*:** Emergency department; ***EHR*:** Electronic health record; ***HDU*:** High dependency unit; ***ICU*:** Intensive care unit; ***MAU*:** Medical admission unit; ***NA*:** Not available; ***NHS*:** National Health Services; ***UK*:** United Kingdom; ***US*:** United States.

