#### Screening and enrolment phases

A staff member will screen patients for eligibility and check their measured vital signs once they arrive at the ED (triage) and the investigator will enroll potentially eligible patients (i.e., age ≥18 years, with suspected infection, and planned for hospitalization). First, a web-based electronic data capture system (EDC) will assign each patient to a participant number in ascending order. Then, the investigator will collect and enter the patient’s initial data (demographics, contact information, Charlson Comorbidity Index (CCI) components, and variables required for qSOFA, SIRS, and EWS scores calculation) in an electronic case report form (eCRF) (see online supplementary materials). If the patient is not eligible, we will close the patient record in the EDC and clarify the cause of exclusion.

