### Data management

We will use an encrypted, web-based EDC (Castor^®^) for this study [27]. Lead investigators (or their delegates) will enter clinical data on an eCRF at each participating center. They will make all entries, corrections, and alterations. The data manager of this study will provide all tools, instructions, and training necessary to complete the eCRF, and each user will be issued a unique username and password.

The monitors will review the eCRFs, evaluate them for completeness and consistency, and compare them with the source documents to ensure no discrepancies. The Monitors cannot enter data in the eCRFs. Lead investigators must verify that all data entries in the eCRF are accurate and correct. If some assessments are not done, or specific information is unavailable, not applicable, or unknown, they must indicate this in the eCRF. Finally, lead investigators must electronically sign off all patients’ eCRF enrolled from their hospitals.

Data manager will lock the final validated database so that no more change will be possible on the frozen data. Subsequently, the principal investigator will receive the patient data (eCRF data + audit trail) for archiving at the investigational site and transference in a secure way to the biostatistical team in Stata format.

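### The rule for confusion of unclear onset has no time limit and no blinding, so the mental-status item of qSOFA and NEWS2 can be revised after triage

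*Protocol article*

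**What the plan says.** Two statements set the time at which predictors are measured. Table 4 gives the time window for PASSEM as "Initial presentation (at triage)". The Predictors section uses "level of consciousness (i.e., first measurement in triage)". The Discussion also presents the use of triage values as a feature of the study.

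The scoring depends on whether the mental state is new. Table 1 gives qSOFA one point for "Altered mental status (GCS <15)", and Predictors narrows this to a new-onset GCS "score of <15 will be considered significant for qSOFA calculation". In Table 2, NEWS2 gives 3 points for new confusion: "thus AVPU becomes ACVPU, where C represents new confusion". NEWS and MEWS in the same table have only alert, voice, pain and unresponsive. SIRS has no mental-status item.

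For unclear cases, Predictors says "we will assume the altered mental state/confusion is new until confirmed otherwise for all scores calculation".

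On data entry, Screening and enrolment phases says that "the investigator will collect and enter the patient’s initial data", and Table 5 marks data collection under enrolment only. Data management says of the lead investigators or their delegates: "They will make all entries, corrections, and alterations". The only freeze described is the final lock. Blinding to outcome is stated only for the diagnosis of infection.

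**The concern.** A predictor fixed at triage cannot also stay open to later correction. As written, the point or points may be removed whenever someone establishes that the confusion is the patient's usual state. That takes time, and a patient who dies early may not have it. Whether the points stay could then depend partly on the outcome that the score is meant to predict.

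The item carries weight: 1 of the 2 points for a positive qSOFA and 3 of the 5 for a positive NEWS2. Because SIRS cannot be affected, any distortion falls on one side of the comparison. The study's hypothesis is that qSOFA has greater prognostic accuracy than SIRS and the early warning scores. A predictor revised with later information would also no longer describe the accuracy available at triage.

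**Working it through.** **Is the window closed elsewhere?** The protocol gives no figure on this point, so the text comes first.

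- Entry at enrolment limits revision but does not exclude it. The flow chart puts a screening phase of 1–2 days before enrolment, so information after triage can already exist at entry.
- The lead investigator extracts predictors from the medical record. In-hospital status, including death, is followed through the patient's record number at the same centre.
- Corrections are allowed until lock, and no blinding covers predictor scoring.

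Later, outcome-aware revision is therefore permitted. Nothing says that it is planned.

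**How large could the effect be?** This is an illustrative calculation for qSOFA only, and every input is an assumption. Items are taken as independent given outcome. Prevalence in deaths versus survivors: respiratory-rate item 50% vs 25%, blood-pressure item 35% vs 12%, truly new confusion 30% vs 8%. A share u of the remaining patients has longstanding confusion of unclear onset, and a share v of these is revised down.

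Probability that the mental-status item is scored: m = p + (1 − p) × u × (1 − v), where p is 0.30 in deaths and 0.08 in survivors. Write m₁ for deaths and m₀ for survivors.

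- Sensitivity at ≥2: 0.175 + 0.50 m₁
- Specificity at ≥2: 1 − (0.03 + 0.31 m₀)
- AUC: 0.687125 [m₁m₀ + (1 − m₁)(1 − m₀)] + 0.932375 m₁(1 − m₀) + 0.307625 (1 − m₁)m₀

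The three AUC constants are the probabilities, with ties counted as half, that a death outscores a survivor when the mental-status items are equal, when only the death has the item, and when only the survivor has it.

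Worked example, u = 5%:

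- No revision: m₁ = 0.30 + 0.70 × 0.05 = 0.335 and m₀ = 0.08 + 0.92 × 0.05 = 0.126. AUC 0.727, sensitivity 34.3%, specificity 93.1%.
- Revised in 80% of survivors and 20% of deaths: m₁ = 0.328 and m₀ = 0.0892. AUC 0.738, sensitivity 33.9%, specificity 94.2%.

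| Revised: survivors / deaths | AUC, u = 5% (vs triage-fixed; vs full revision) | AUC, u = 10% (vs triage-fixed; vs full revision) |
|---|---|---|
| None (triage-fixed) | 0.727 | 0.721 |
| 100% / 100% (full revision) | 0.734 (+0.006; 0) | 0.734 (+0.012; 0) |
| 80% / 80% | 0.732 (+0.005; −0.001) | 0.731 (+0.010; −0.003) |
| 80% / 50% | 0.735 (+0.008; +0.001) | 0.736 (+0.015; +0.003) |
| 80% / 20% | 0.738 (+0.011; +0.004) | 0.742 (+0.021; +0.008) |
| 50% / 80% | 0.728 (under +0.001; −0.006) | 0.722 (under +0.001; −0.012) |
| 20% / 80% | 0.723 (−0.004; −0.011) | 0.712 (−0.009; −0.021) |

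With u = 2%, the 80% / 20% pattern adds 0.004 against the triage-fixed score and 0.002 against full revision. With u = 10% in deaths and 5% in survivors, the triage-fixed AUC is 0.736 and the 80% / 20% pattern gives 0.745, which is +0.009 against triage-fixed and +0.011 against full revision.

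**How much of this comes from dependence on outcome?** Compare 80% / 20% with 80% / 80%: 0.7376 − 0.7322 = 0.005 at u = 5%, and 0.7418 − 0.7309 = 0.011 at u = 10%. The rest of the gain over the triage-fixed score comes from using later information at all.

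**The case against.** The strongest reply is that the rule is only a default for unclear cases at enrolment. Level of consciousness comes from triage, the variables are entered as initial data, and Table 5 marks data collection at enrolment only. The permission to correct entries is ordinary data management, with source checks by monitors. This stands as a reason to expect little revision. It does not close the window, because the rule has no deadline and no blinding.

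Three stronger readings are tempting, and the document does not support them.

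- *Survivors are revised more often, so the scores are inflated.* A reader might infer this from the time that confirmation takes, but nothing in the protocol says it. The primary outcome is 30-day in-hospital death, so not all deaths are early, and records can show a usual state whatever the outcome. In the table, reverse revision patterns reduce the AUC against full revision.
- *Every score except SIRS is affected.* By Table 2, an alert but confused patient scores 0 on that item in NEWS and MEWS. Only qSOFA and NEWS2 clearly depend on whether confusion is new. The other two are reached only through the rule's extension to all scores.
- *Dozens of patients would be wrongly reclassified.* Take 2,851 × 74/879 = 240 deaths and 2,611 survivors. Assume 3–10% unclear cases, the item decisive in 25–50% of them, and revision in 60% of survivors and 20% of deaths. The net count is 2,611 × 0.0045 − 240 × 0.0015 = 11, up to 2,611 × 0.030 − 240 × 0.010 = 76. Equal revision of 60% already gives 2,371 × 0.0045 = 11, up to 2,371 × 0.030 = 71. The outcome-dependent part is only 240 × 0.03 × 0.25 × 0.4 = 0.7, up to 240 × 0.10 × 0.50 × 0.4 = 4.8 patients. Such a count does not measure outcome-dependent bias.

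It can also be said that SIRS needs a white cell count, so the comparator is not purely triage-based. That is fair, but the initial count is not subject to a rule of this kind.

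**Conclusion.** The point holds in a limited form. The protocol fixes the predictors at triage but leaves one item open to later, unblinded revision, and that item enters qSOFA and NEWS2 but not SIRS. If survivors are clarified more often than patients who die early, the comparison tilts towards qSOFA and NEWS2.

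The size is probably small. The largest upward shift in these qSOFA scenarios is 0.011 against full correct revision and 0.021 against a triage-fixed score. Both the size and the sign rest on inputs that the document does not give: the share of unclear cases, the revision rates by outcome and the item prevalences. NEWS2 was not modelled. This is a cheap improvement to make, and it does not show that the study's comparison is invalid.

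**What to change.** For the primary score calculation, settle new versus usual confusion only from information available at triage. Score unclear onset as new and do not revise it afterwards. Record any later clarification in a separate eCRF field, judged blind to outcome, and use it only in a sensitivity analysis. Reconcile the rule's extension to all scores with Table 2, either by limiting it to qSOFA and NEWS2 or by stating how it applies to NEWS and MEWS.

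The cost is about one sentence and one eCRF field. The downside is that some patients with longstanding confusion keep their points, which would usually lower the apparent accuracy of qSOFA and NEWS2 slightly. In the qSOFA calculation with equal shares of unclear cases in both outcome groups, the AUC falls from 0.734 under full revision to 0.731, 0.727 and 0.721 at 2%, 5% and 10%. With more such cases among deaths (10% vs 5%) it does not fall (0.736). The sensitivity analysis would show the difference.
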